### 4.3. Assessments

Patients will be jointly evaluated by the pulmonology and otorhinolaryngology services of the hospital.

Evaluation by a pulmonology specialist: A detailed medical history is taken to record symptoms and risk factors associated with sleep apnea. BMI is calculated, and questionnaires that assess daytime sleepiness (the Epworth test; Appendix A) and sleep quality (the Pittsburgh questionnaire; Appendix B) are administered. Patients suspected of having sleep apnea undergo either polysomnography or diagnostic respiratory polygraphy based on their clinical symptoms. After this first assessment, the pulmonologist refers the patient to the otorhinolaryngology department to assess the anatomy and functionality of the upper airways. Patients with a BMI of >30 are transferred to the nutrition and dietetics unit. It is known that a reduction in BMI of 5–10% significantly reduces the AHI [32].

The sleep study is performed using standard polysomnography.

Standard nocturnal polysomnography involves (i) recordings of sleep-related electroencephalography (EEG), electromyography (EMG) of the chin and leg muscles, electrooculography (EOG), and electrocardiography (ECG); (ii) oxygen saturation; and (iii) measures of respiratory effort and airflow.

The tests are used to define PS with an AHI of <5 events/h of sleep, moderate OSAHS as an AHI of 15 to 29.9 events/h of sleep, and severe OSAHS as ≥30 events/h of sleep [eleven].

Laboratory-assisted polysomnography has been and continues to be a gold standard for the diagnosis of sleep-disordered breathing, although the usefulness of a single night-time recording for diagnosis can generate considerable variability in the AHI from night to night, especially when the AHI is low [11].

Therapy with the AirwayGym^®^ application will be initiated after inclusion in this study. This therapy will be applied to patients with an average duration of training of 5 days a week with 15–20 min/session. Three months after myofunctional therapy, an otorhinolaryngological evaluation, sleep questionnaires, and tongue strength measurements with the IOPI and ultrasound will be performed [11].

Evaluation by an otorhinolaryngology specialist: The otorhinolaryngology specialist is responsible for the anatomical and functional examination of the upper airways. During this consultation, the Friedman stage and Müller maneuver are assessed, and nasofibrolaryngoscopy is performed to determine the degree of retropalatal and/or retrolingual collapse. Subsequently, functional evaluation is performed using the IOPI Medical Device to assess tongue strength by measuring the maximum pressure and tongue fatigue by measuring resistance. Low resistance values indicate a high tendency to fatigue, in which case patients would benefit from treatment modulation with the AirwayGym app.

Another instrument for measuring tongue tone is the tongue digital spoon (TDS), which has recently been applied for the diagnosis and evaluation of patients with sleep apnea and lingual hypotonia [33,34]. In addition to telemedicine follow-up, patients will be provided with a sleep diary for symptom control (Appendix C to evaluate the response and adherence to therapy with the AirwayGym app. After this consultation, the patient will be offered DISE and cervical ultrasound to optimize the selection of the current treatments for sleep apnea [35].

The distribution of visits to the center will be as follows:Pulmonology visit: Patients will be diagnosed with OSA in a pulmonology laboratory via an initial sleep study, which includes the measurement of baseline AHI, the nocturnal desaturation index, and the lowest oxygen saturation levels during the night.Otorhinolaryngology visit: Patients will be assessed by the otorhinolaryngologist, who will evaluate the anatomy and functionality of the upper airways using DISE and measure tongue strength with the IOPI and TDS. The AirwayGym app is recommended for patients with oropharyngeal hypotonia.Ultrasound visit: A neck ultrasound will be performed to measure tongue thickness (mm), height (mm), volume (cm^3^), and distance between the lingual arteries (mm) before DISE and at the start of treatment modulation with the app (Figure 4 and Figure 5).Monthly telemedicine follow-up: During the 3-month study period, all patients in the three groups will be monitored for adherence and incidents related to the prescribed treatment with the AirwayGym app.Three-month follow-up: All variables evaluated during the initial visit will be measured again after three months. The ultrasound visit is an evaluation added to this previously published protocol (Tongue +) [36]. A submental ultrasound will be performed in the context of sleep apnea.

The Kolmogorov–Smirnov test will be used for the distribution of quantitative variables. The chi-square test or Fisher test will be used as necessary for the study of categorical variables. Student’s *t*-test or ANOVA (for two or more samples) will be used to study the differences between quantitative variables.

Non-parametric tests (Mann–Whitney or Kruskal–Wallis) will be used if the variables to be analyzed do not follow a normal distribution. The level of statistical significance will be set at *p* < 0.

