### 2.2. Study Groups

The control group will include patients with recent moderate–severe sleep apnea (1–3 months) undergoing treatment with continuous positive airway pressure (CPAP) therapy. An initial ultrasound measurement of the tongue genioglossus fat will be made and 3 months after inclusion in this study.

The MT group will include patients with moderate apnea. MT exercises alone, once a day for 3 months, will be performed exclusively via the AirwayGym app. An initial ultrasound measurement and drug-induced sleep endoscopy (DISE) will be performed with repeated control at 3 months.

In the MT-CPAP severe apnea group, patients will use CPAP at night, measuring the number of hours they use it at night. A new sleep study will be performed at 3 months. An initial ultrasound measurement and DISE will be made with control at 3 months (Figure 1).

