### 2.3. Objectives

-To evaluate the influence of MT on the reduction in cervical fat and the improvement of ultrasound parameters in sleep apnea.-To measure different parameters related to the function and size of the genioglossus and geniohyoid muscles to evaluate the presence and severity of sleep apnea, as well as the effectiveness of myofunctional therapy in improving the function of these muscles.-To determine whether performing a neck ultrasound is relevant for the indication of TM in sleep apnea.-To evaluate whether performing ultrasound and DISE modify the indication of surgical techniques compared with if we only performed DISE.-To evaluate the adherence to CPAP and MT.

The hypothesis of our work is based on determining whether knowledge of the fatty and muscular components can be decisive in the choice of pharyngoplasty techniques, in multilevel surgery, and as a possible predictor of response or failure to MT since, currently, the influence that TM can have on reducing cervical fat is unknown.

Given that the aforementioned tools only measure strength, we consider the previous study of cervical fat using ultrasound and its response to TM relevant in the study of collapse patterns during DISE.

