## 5. Expected Results

MT is a promising treatment for sleep apnea [37,38]. The AirwayGym app [39] is a mobile app for delivering MT using exercises aimed at strengthening the oropharyngeal muscles. Patients are instructed to perform the MT exercises for 20 min daily for at least 3 months. In most MT programs delivered without a smartphone, patients complete the exercises independently at home without feedback from the therapist. The main drawback of this type of MT is low patient adherence, which has been reported to be as low as 10% in some studies [40,41]. Baptista et al. [41] note that most existing mobile health apps for OSA have focused on the diagnosis of snoring or OSA. Smartphone technology can be valuable for treating people with OSA and for conducting MT.

When using this protocol, in addition to reinforcing the need for apps to promote adherence to MT in sleep apnea, we consider it necessary to clinically monitor the anatomical changes that occur during therapy because excess soft tissue surrounding the upper airways can contribute to a narrow and collapsible airway. However, the effects of parapharyngeal fat deposits at different levels on the severity of OSA remain unclear [20,21]. DISE provides accurate vision and evaluation of the site of the collapse of the upper airways under conditions that better approximate natural sleep than with the patient awake [18].

The objective of myofunctional therapy is to improve adherence to CPAP treatment since this monotherapy, despite its high effectiveness, has a low compliance rate.

Another objective set in this therapy is to carry out simple measurements for a better diagnosis and treatment [42].

Ultrasound is a non-invasive, low-risk, and cost-effective imaging modality that can also be used to assess the tongue. Submental ultrasound can be used to characterize the tongue in people with OSA and has shown that increased tongue width and thickness are associated with severe OSA. Ultrasound can also show dynamic movement that characterizes the changes in tongue morphology with activities such as the Müller maneuver [17,18,43]. Yu et al. [19] reported that ultrasound echo intensity increases with increased tongue fat content and strongly correlates with tongue fat measurements in MRI. Given that the IOPI and TDS measure only tongue strength, we consider it important to also measure cervical fat using ultrasound to clinically assess the responses to the AirwayGym app.

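### Adherence is a stated objective, but the exercise schedule appears in two incompatible frequencies and no common method of recording CPAP hours is secured for the two CPAP groups

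*Protocol article*

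**What the plan says.** The last objective in Section 2.3 is "To evaluate the adherence to CPAP and MT". Section 5 goes further: "The objective of myofunctional therapy is to improve adherence to CPAP treatment".

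The exercise schedule appears in three places:

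- Section 2.2, for the MT group: "MT exercises alone, once a day for 3 months, will be performed exclusively via the AirwayGym app". No session length is given.
- Section 4.3: "This therapy will be applied to patients with an average duration of training of 5 days a week with 15–20 min/session".
- Section 5: "Patients are instructed to perform the MT exercises for 20 min daily for at least 3 months".

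The Section 2.2 description of the MT-CPAP group gives no exercise frequency.

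On CPAP use, Section 2.2 states: "In the MT-CPAP severe apnea group, patients will use CPAP at night, measuring the number of hours they use it at night". It does not say how the hours are obtained. The control group is also on CPAP, but its description in the same section mentions only the two ultrasound measurements. The visit list in Section 4.3 says that patients in all three groups "will be monitored for adherence and incidents related to the prescribed treatment with the AirwayGym app". Section 4.3 also gives patients a sleep diary without limiting it to a group, and the Appendix C diary has an item on hours of CPAP use and one on completion of the exercises. Section 4.2 says that exercise results are stored online and can be reviewed by a therapist. Its list of variables contains no adherence measure.

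**The concern.** A percentage adherence needs one prescribed quantity as its denominator. The article supplies two that cannot both hold, so the same patient record yields different results on a listed objective depending on the section the analyst reads. The schedule also defines the intervention. Therapists following different sections could prescribe different amounts of exercise, which would then be mixed within one group.

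On the CPAP side, any statement about CPAP use with and without MT needs hours obtained in the same way in both CPAP groups. The article names the measurement for one group and leaves it implicit for the other. If the hours come from different sources, a difference between groups could reflect the way they were recorded.

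**Working it through.** The article states no adherence figure, and the 15 patients per group are a pilot choice without a formula, so there is no figure to reproduce. The check is arithmetic on the stated schedules.

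**Inputs**

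- Daily frequency: 7 sessions a week (Sections 2.2 and 5).
- Five-day frequency: 5 sessions a week of 15–20 min (Section 4.3).
- Session length under the daily schedule: 20 min (Section 5).
- Length of 3 months: 13 weeks. This is an assumption.

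**Prescribed sessions** = sessions per week × weeks

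- Daily: 7 × 13 = 91.
- Five days a week: 5 × 13 = 65.
- Ratio: 65 / 91 = 0.714, or 91 / 65 = 1.40 the other way. With 12 weeks the counts are 84 and 60, and the ratio is the same.

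**Prescribed minutes**

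- Daily: 7 × 20 = 140 a week; 140 × 13 = 1,820 in total.
- Five days a week: 5 × 15 = 75 to 5 × 20 = 100 a week; 975 to 1,300 in total.
- Ratio: 140 / 100 = 1.40 to 140 / 75 = 1.87.

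**Adherence** = completed sessions / prescribed sessions

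| Completed sessions | Against 91 (daily) | Against 65 (5 a week) |
|---|---|---|
| 52 | 57.1% | 80.0% |
| 65 | 71.4% | 100% |
| 91 | 100% | 140% |

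**CPAP hours, passages side by side**

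| Place | MT-CPAP group | Control group |
|---|---|---|
| Section 2.2 | Nightly hours measured, method not named | Hours not mentioned |
| Section 4.3, monthly follow-up | Adherence monitored in relation to the app | Included, but monitoring is tied to an app this group is not described as using |
| Section 4.3 and Appendix C, diary | Self-reported hours possible | Self-reported hours possible, but Section 4.3 links the diary's adherence purpose to the app |

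Self-reported hours can therefore be obtained in both groups. No passage says that the same source will be used in both.

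**The case against.** The strongest reply is that the conflict is smaller than three passages suggest. Sections 2.2 and 5 agree on daily exercise, and Section 5 only adds a session length and an open-ended minimum duration. Section 4.3 speaks of an average, which might describe expected rather than prescribed use. The first part stands: there are two incompatible frequencies, not three. The second is possible, but Section 4.3 presents the five days as how the therapy will be applied and does not call it a forecast. For the MT-CPAP group, only Sections 4.3 and 5 bear on frequency, and they disagree.

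A second reply is that an article need not carry a full definition of adherence, and that the Section 4.2 list is plainly not exhaustive, since it also omits the sleep questionnaires and tongue volume, which are planned elsewhere. This stands too. The absence of an adherence variable from that list does not show that adherence goes unrecorded. Condensation does not, however, explain two different frequencies printed in one document.

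Some stronger readings are tempting but not supported:

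- A reader might infer that neither adherence can be computed. The app record and the diary can supply completed sessions, and the diary can supply CPAP hours. What is undetermined is the MT denominator and a common CPAP source.
- A reader might infer that controls have no measured CPAP comparator, or that MT-CPAP hours are read from the machine. The diary is not restricted by group, and Section 2.2 names no method. Hours in both groups might come from the diary.
- A reader might infer that controls have already lost patients who gave up CPAP early. The 1–3 months in Section 2.2 may date the diagnosis rather than CPAP use, and the inclusion criteria only cap controls' earlier treatment at 3 months.

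**Conclusion.** The point holds in this limited form. The article gives two incompatible exercise frequencies, differing by a factor of 1.4 in sessions and 1.4 to 1.87 in minutes. For a patient completing 65 sessions, adherence moves between 71% and 100%. The session counts rest on 13 weeks; the ratios do not. They also rest on reading Section 4.3 as a prescription, which its wording favours but does not settle.

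For CPAP, the finding is that a common method is not secured across the two CPAP groups, not that data are absent. Even with a common method, a comparison of CPAP hours would not isolate an effect of MT. The study is not randomised, MT-CPAP patients have severe apnea while controls are moderate to severe, and earlier CPAP exposure may differ. The correction should be made because adherence is a stated objective and the contradiction is cheap to remove.

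**What to change.** 1. The investigators should reconcile Sections 2.2, 4.3 and 5 into one exercise schedule that applies explicitly to both MT groups. Which schedule is a clinical decision, on which no view is taken here. If the Section 4.3 figure is meant as expected use, the text should say so.
2. Use the prescribed number of sessions over the 3 months as the fixed denominator for MT adherence, and take completed sessions from the app record.
3. Name one method for recording nightly CPAP hours and apply it over the same 3 months in the control and MT-CPAP groups.
4. Add both measures to the variable list in Section 4.2.
5. Report any comparison of CPAP hours between the two groups as descriptive only. Adjusting for days already on CPAP would not rescue it: if controls enter on CPAP and MT-CPAP patients start at inclusion, that covariate would barely overlap between groups of 15, and severity would still differ.

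The cost is mostly wording, plus collecting CPAP hours in controls at contacts already planned. No extra patients or visits are needed.

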MRI is the most commonly used imaging method to measure volumes and obstruction in the upper airways. Recent studies have incorporated computed tomography with the patient under sedation [14] and ultrasound. Ultrasound is a non-invasive, low-risk, and cost-effective imaging modality that can also be used to assess the tongue. Submental ultrasound can be used to characterize the tongue in patients with OSA and has shown that an increased width and thickness of the tongue are associated with severe OSA [15,16]. Ultrasound can also be used to examine the dynamic movements that characterize changes in tongue morphology with activities such as the Müller maneuver [17,18]. Yu et al. [19] reported that the ultrasound echo intensity increases with increasing fat content in the tongue and strongly correlates with tongue fat measurements in MRI.

In the context of OSA, submental ultrasound can be used to determine whether the size of the tongue muscles is adequate to keep the upper airways open during sleep. Small or weak muscles may increase the risk of airway obstruction and sleep apnea [20]. MT can increase the size and strength of the genioglossus and geniohyoid muscles, which helps to improve upper airway function and reduce the severity of OSA.

Myofunctional therapy (MT) is based on oropharyngeal exercises that try to obtain a proper tongue positioning in the oral cavity. Guimaraes [21] in his randomized clinical trial (RCT) demonstrated that oropharyngeal exercises reduced the OSAS severity from an apnea–hypopnea index (AHI) of 22.4 +/− 4.8 to 3.7 +/− 8.5 events/hour. MT is composed of isotonic and isometric exercises that target oral structures (i.e., the lips and tongue) and oropharyngeal structures (i.e., the soft palate and lateral pharyngeal wall). There has been an increasing number of studies evaluating the effect of MT in the form of case studies, case series, and, most recently, two RCTs [12,22,23,24,25,26]. Because MT raises serious concerns relating to adherence, our sleep unit has designed the AirwayGym app to perform these exercises.

Using this protocol, we can examine the usefulness of ultrasound in predicting the treatment response to MT delivered by specialists using the AirwayGym application employed in our sleep unit.

The AirwayGym application was created in 2018 by the Sleep Units of the Quiron Salud Marbella and Campo de Gibraltar Hospital together with the computer engineering departments and developed by the apnea company Bye.

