The novelty of this application is that the patient carries out his therapy from home with his smartphone, providing him with feedback on the effectiveness of the exercises that can also be supervised by his therapist. Complete information about the application is provided at https://airwaygym.App/ (accessed on 27 January 2024). Every therapist can sign up and track their patients [27].

The objective is to conduct a prospective, non-randomized pilot study in patients with moderate–severe obstructive sleep apnea–hypopnea syndrome (OSAS).

We measure with ultrasound the thickness of the lingual and pharyngeal walls, the distance between both lingual arteries, and the height and lingual volume in the patients included in this study.

The desired impact is to improve adherence to CPAP and myofunctional therapy, as well as perform simple anatomic evaluations such as ultrasound. If this improves treatment adherence and can diagnose and treat these patients in the future, there is ample scope for further clinical trials.

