## 3. Materials and Equipment

To develop the protocol, patients with sleep apnea were included who underwent submental cervical ultrasound and DISE before starting the AirwayGym App and after 3 months of treatment.

The measurements were made with the convex probe of the FUJFILM Sonosite LX ultrasound.

In submental ultrasound in the context of sleep apnea, different parameters can be measured to evaluate the size and function of the genioglossus and geniohyoid muscles, which are important for keeping the upper airway open during sleep. Some of the parameters that can be measured in submental ultrasound are:Genioglossus and geniohyoid muscle thickness: The thickness of the genioglossus and geniohyoid muscles can be measured at different points on the lower part of the jaw. A smaller thickness may indicate weakness or atrophy of these muscles.The cross-sectional area of the genioglossus and geniohyoid muscles: The cross-sectional area of the genioglossus and geniohyoid muscles can be measured at different levels of the lower jaw. A smaller cross-sectional area may indicate a decrease in the size of these muscles.Tongue movement distance: The tongue movement distance forward from the rest position can be measured. A shorter movement distance may indicate weakness in the muscles that control the position of the tongue.

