### 4.2. Definition of Variables

The variables that we will measure in all patients and that are reflected in the data collection table using IBM SPSS Statistics version 28 with Windows software are as follows:Age;Sex;Weight;Height;BMI;Abdominal circumference (at the level of the navel);Neck circumference (with a flexible tape on the most prominent part; for this, it is necessary for the patient to be standing, with arms hanging at the sides, head erect, and gaze forward);Measurement with IOPI of tongue force and buccinator muscle;Measurement with digital spoon (DS);Initial AHI;Ranking of velum, oropharynx, tongue base, and epiglottis (VOTE) in DISE, before and after;Ultrasound measurements: echo intensity, tongue height (mm), and tongue width (mm).

To develop the protocol, patients with sleep apnea underwent submental cervical ultrasound and DISE before starting to use the AirwayGym app (www.airwaygym.app, accessed on 27 January 2024) and after 3 months of treatment.

The AirwayGym app is a portable fitness app (Figure 2) intended for patients rather than athletes, and therapists rather than coaches provide the instructions. The novelty of this app is that it is the first healthcare app on the market that allows patients to directly interact with a smartphone without the need for any other device. The app focuses on improving proprioceptive deficits in patients with sleep apnea. When used with the app, the smartphone provides acoustic feedback on the effectiveness of the MT exercises performed [27].

The AirwayGym app comprises daily tension and concentration exercises (i.e., isometric and isotonic exercises, respectively) that can be performed anywhere. It offers the additional advantage of providing prompt feedback to allow patients to see their progress and resolve problems with the help of a therapist. Before each exercise, an animated demonstration and video provide instructions for performing the exercise. After each exercise, patients receive visual, acoustic, and tactile feedback as a score on the success of their performance. A chat function is available via which patients can contact the therapist directly. This app complies with regulations 2002/58/EC and (EU) 2016/679 regarding data protection. It is priced at EUR 8.99. Additional information can be found on the AirwayGym website.

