### 5.1. Preliminary Results

Additionally, submental ultrasound may be useful to evaluate the effectiveness of MT in sleep apnea. Studies have shown that myofunctional therapy can increase the size and strength of the genioglossus and geniohyoid muscles, which can improve upper airway function and reduce sleep apnea. Submental ultrasound can be used to measure these muscle changes and evaluate the effectiveness of therapy. With 10% of the patients included, there were significant differences (*p* < 0.05) in the initial volume (mm^3^) and lingual thickness (mm) between the control patients and the patients in the groups with moderate–severe sleep apnea. After 3 months of myofunctional therapy, we found a statistically significant improvement in the values of the functional examination with IOPI and the digital spoon and a reduction in lingual thickness (mm) of >15% in the patients studied.

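### The ultrasound visit and the data table list different measures, so it is uncertain whether fat and muscle size will be recorded

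*Protocol article*

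**What the plan says.** The first objective in 2.3 is "To evaluate the influence of MT on the reduction in cervical fat and the improvement of ultrasound parameters in sleep apnea". The second concerns the function and size of the genioglossus and geniohyoid muscles.

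The protocol article states in several places what the ultrasound measures, and the places differ:

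- 4.3 Assessments, ultrasound visit: "A neck ultrasound will be performed to measure tongue thickness (mm), height (mm), volume (cm^3^), and distance between the lingual arteries (mm").
- 4.2 Definition of Variables, introduced as "The variables that we will measure in all patients and that are reflected in the data collection table": "Ultrasound measurements: echo intensity, tongue height (mm), and tongue width (mm").
- 1. Introduction: "We measure with ultrasound the thickness of the lingual and pharyngeal walls, the distance between both lingual arteries, and the height and lingual volume". The Abstract names thickness, volume and lingual-artery distance. Neither includes echo intensity among the study's measurements.
- 3. Materials and Equipment describes genioglossus and geniohyoid thickness and cross-sectional area, and tongue movement distance, as things that ultrasound can measure. It does not say that they will be measured.

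The Introduction and section 5 both cite a study in which echo intensity rose with tongue fat and agreed with MRI. No other listed ultrasound measure is linked to fat.

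On direction, the Introduction says that "MT can increase the size and strength of the genioglossus and geniohyoid muscles", and section 3 says of these muscles that "A smaller thickness may indicate weakness or atrophy of these muscles". The Introduction and section 5 also associate a wider and thicker tongue with severe OSA, and 5.1 reports "a reduction in lingual thickness (mm) of >15% in the patients studied" after therapy.

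**The concern.** The visit description tells the operator what to read from the scan, and the data table tells the study what to record. If the visit description is followed, no fat index is taken. If the data table is followed, thickness, volume and artery distance have nowhere to go. Neither list holds a muscle-specific size.

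Two of the study's objectives depend on this. A change in fat needs a fat index at baseline and at 3 months in every group. A change in muscle size needs a muscle measurement. Whole-tongue thickness and volume contain both tissues. A fall could be fat loss or muscle loss, and a rise could be muscle gain or fat gain. Without tissue-specific measures and a stated direction for each, a size change can be given a meaning after the result is known.

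**Working it through.** The article gives no figure to reproduce, and no error-rate or sample-size formula applies. The check is an item-by-item comparison of the lists.

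| Measure | Visit (4.3) | Data table (4.2) | Abstract | Introduction |
|---|---|---|---|---|
| Tongue thickness | yes | no | yes | yes |
| Tongue height | yes | yes | no | yes |
| Tongue volume | yes | no | yes | yes |
| Lingual-artery distance | yes | no | yes | yes |
| Echo intensity | no | yes | no | no |
| Tongue width | no | yes | no | no |
| Genioglossus/geniohyoid thickness or area | no | no | no | no |

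(The Introduction also lists pharyngeal wall thickness, which is in neither 4.2 nor 4.3.)

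**Overlap of the two operative lists.** The visit has 4 items and the table 3, with 1 shared (height), so the union is 4 + 3 − 1 = 6. Absent from the table: 4 − 1 = 3 of the 4 visit items. Absent from the visit: 3 − 1 = 2 of the 3 table items.

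**Sensitivity to naming.** Suppose thickness and width are two names for one dimension. This is an assumption, and the Introduction lists them separately. The overlap becomes 2, the union 4 + 3 − 2 = 5, and 2 of the 4 visit items are still absent from the table. Echo intensity is still absent from the visit.

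**Is fat measured in each group at both times?** Section 2.2 plans an ultrasound measurement of genioglossus fat in the control group, at the start and at 3 months, without naming the method. For the two myofunctional therapy groups it mentions only an ultrasound measurement at those times, with no reference to fat. The 3-month visit in 4.3 repeats what was evaluated initially, so an item not read at baseline has no change score. Whether the therapy groups have a fat change therefore depends on which of 4.2 and 4.3 is followed.

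**Can size stand in for fat or muscle?** The statements that larger is better and that thinner suggests atrophy concern the genioglossus and geniohyoid. The statement that thicker is worse concerns the tongue as a whole. All can hold if fat falls while muscle grows. To show that, one needs a fat index and a muscle size. The visit list has neither, and the data table has only the fat index.

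**Consistency with the reported results.** Section 5.1 gives results for lingual thickness and volume, neither of which is in the data table, and gives no echo intensity result. It states volume in mm³, whereas the Abstract and 4.3 use cm³.

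**The case against.** The strongest reply is that the fat measure is in the plan. Section 4.2 lists echo intensity for all patients, 2.2 plans a genioglossus fat measurement in controls, 4.3 repeats the initial variables at 3 months, and section 5 states the intention to measure cervical fat by ultrasound. This stands. A reader might infer from the visit list that the fat objective cannot be answered at all, and the article does not support that reading. What remains is that two operative lists disagree on whether the fat index is taken.

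A reader might also infer that the article counts both a smaller and a larger tongue as success, so that the hypothesis cannot fail. That goes too far. The two directions refer to different structures. In 5.1 the word improvement attaches to the IOPI and digital spoon values, and the fall in thickness is a separate result. No success rule accepts a change in either direction. Because the text says that higher echo intensity means more fat, the fat objective can fail if echo intensity is recorded and does not drop. The gap is one of interpretation: no muscle-specific size is listed, and no expected direction is fixed for each measure.

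It is also fair to say that section 3 does name the muscle measures. It presents them as possible measurements, and neither 4.2 nor 4.3 takes them up.

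Finally, this is a pilot of 15 patients per group, and a journal article condenses. Condensation could explain a short list. It does not explain two lists that differ.

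**Conclusion.** The point holds as an inconsistency that should be fixed. The visit list and the data table share 1 of 6 measures, or 2 of 5 if thickness and width are the same thing. The only listed measure linked to fat is missing from the visit, and muscle-specific size is missing from both lists. As written, the fat and muscle-size objectives cannot be reliably answered: fat data at both times in all groups are uncertain, and whole-tongue changes such as the fall of more than 15% in 5.1 cannot be assigned to fat or to muscle.

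This rests on reading 4.2 and 4.3 as the lists that govern data collection, and section 3 as a description of what is possible. One limit remains even after reconciliation: the article ties echo intensity to tongue fat, while the objective names cervical fat.

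**What to change.** Use one ultrasound list, identical in 4.2 and 4.3, for all three groups at baseline and at 3 months, and bring the Abstract, the Introduction and section 3 into line with it:

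- Fat: echo intensity, read at the same probe settings at both visits, with a decrease expected. State that it indexes tongue fat, not cervical fat as a whole.
- Muscle: genioglossus and geniohyoid thickness or cross-sectional area, with an increase expected.
- Whole tongue: thickness, height, width, volume and lingual-artery distance, kept as descriptive measures and assessed two-sided, with the expected direction for whole-tongue size stated separately from the two above.
- Volume: one unit throughout.

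The cost is a few more readings from a scan that is already planned, with no added procedure. The real downside concerns patients already scanned: their baseline images may not yield a usable echo intensity, and rewording cannot recover it. Those values should be reported as missing.
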